## 2. Methods

The protocol of this study is following the guidance of CONSORT [30]. The methods are categorised into subsections presented below (see Supplementary File S1).

### 2.1. Study Location

Saudi Arabia will be the location of this study. The trial will only be conducted at one site, namely the obesity, endocrine, and metabolism centre at King Fahad Medical City (KFMC), the hub of the Riyadh Second Health Cluster. KFMC is one of Saudi Arabia’s most significant and well-known medical cities, which serves the country’s largest medical complex.

### 2.2. Trial Design

The present study will adopt a double-blind randomised two-arm feasibility trial to investigate the feasibility of a 3-month intervention for participants who have had difficulty managing their T2DM. Mixed methods will be employed in the study’s design to gather and analyse both quantitative and qualitative data. A mixed methods approach allows the study to address additional research questions [31]. An RCT will be used since it is the best design for comparing the effectiveness of health coaching between the two groups [32]. The primary and secondary trial outcomes will be examined using various approaches, including questionnaires, interviews, focus groups, and clinical measures, to assess the intervention’s feasibility, acceptability, and preliminary effects. The study evaluation will be conducted at two points: at the intervention’s baseline and three months following the intervention (endpoint). To conduct this study, ethical approval was obtained by the University of Sheffield and the Institutional Review Board (IRB) committee form ethical approval at (KFMC) (IRB Log Number: 21-062E). The CONSORT flow diagram will describe the route participants take through the health coaching intervention, including the schedule of enrolment, interventions, and assessments [33].

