### 2.6. Randomisation and Blinding

All recruited participants will be randomised on a 1:1 ratio into one of two groups. The randomisation process will be carried out by an independent person out of this study and used a computer to generate random numbers. To minimise selection bias, eligible participants will have an equal opportunity of being allocated to each group. The researchers will remain unaware of which group a participant had been assigned to before the baseline assessment. Participants will be informed which group they have been assigned to after the baseline assessment.

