#### 2.8.2. Intervention Procedure

Three trained and qualified health coaches will deliver the coaching sessions. They all will receive training on the intervention curriculum (see Table 2). Additionally, they will be monitored by the researchers throughout the period of delivery of the intervention. The intervention consists of 6 sessions that will be delivered biweekly via face-to-face meetings and telephone coaching over a 3-month period. Intervention group participants will be contacted fortnightly and coached using a combination of different methods; in person, by phone, and by smartphone (e.g., secure messaging such as WhatsApp) while the control group participants only receive the usual care for participants with T2DM with includes general lifestyle advice. Face-to-face coaching is only conducted at baseline and in the third month of the intervention for 30–45 min coaching sessions. In addition, 10–15 min telephone coaching will be delivered for the other four sessions (see Figure 1). 

The health coach works as an ally to enable participants to effectively engage in their self-care needs and address potential self-management barriers. They will be provided with different tools, including a patients’ progress tracker, coach notes log and a coaching log to help them run each coaching session. Participants will be given the opportunity to learn and practice significant skills to help them reach target goals through action plans they set for themselves for better self-care [43]. Table 2 illustrates the operationalised protocol and phases of session delivery

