#### 2.8.3. Usual Care (Control Group)

Control group participants will receive only the usual care. Standard care includes providing written information on diabetes and brochures for raising awareness, including the benefits of modifying their health behaviours. Generally, T2DM patients have regularly scheduled visits to check diabetes management by endocrine specialists. The visit’s main purpose is to check whether the patient’s medications need to be replaced, increased, or continue with the same prescription.

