### 2.9. Measures

Different tools and measures will be used to assess the primary and secondary study’s outcomes as presented in below sections. To reduce the risk of bias, an independent interviewer will be trained and supervised by the researchers to undertake the role of collecting some data, including semi-structured interviews and providing questionnaires. The interview guide will be developed by the researchers and used by the interviewer to guide the interviews. The interviewer will remain blind to the intervention details, process, and activities. Control group participants will be requested to complete pre- and post-intervention measures and questionnaires.

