Qualitative data, including interviews, focus groups, meetings, and coaching sessions will be recorded on electronic recorders, transcribed, and translated. There will be interview guidance used to direct the conversations and enable the researchers to obtain the intervention’s information. All participants will be given a unique reference number used when referring directly to their responses. Quantitative data will be generated and collected by the researchers with support from the centre’s health professionals, including HbA1c, BMI, blood pressure, weight and waist circumference. All data will be encrypted using a high-level encryption method to protect collected data (using FileVault on Mac) and the University Data Centre.

The researchers will be monitoring the quality of data from the beginning until the intervention endpoint. Data will be organised based on its type (e.g., interviews, coaching sessions, etc.), in separate files within one folder for easy access to each type at any time. Multiple copies of the folder will be backed up and stored throughout the period of data collection. Backups with up-to-date data will be completed continuously to keep data safe and updated. Qualitative data will be recorded to avoid accidentally missing information. This would allow for assessing the consistency and quality of the data collected. Vitro measures will be taken by a health practitioner (e.g., laboratory specialist) from KFMC in Riyadh. Multiple samples will be taken to ensure the quality of results by comparison.

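### Section 2.2 labels the trial double-blind, but participants are told their group and no role is stated to be blind to allocation after baseline

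*Protocol article*

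**What the plan says.** Section 2.2 (Trial Design) fixes the design: "The present study will adopt a double-blind randomised two-arm feasibility trial".

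Section 2.6 (Randomisation and Blinding) makes two statements on who knows the allocation. For researchers: "The researchers will remain unaware of which group a participant had been assigned to before the baseline assessment". For participants: "Participants will be informed which group they have been assigned to after the baseline assessment". It says nothing about blinding during follow-up.

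Section 2.8.2 describes delivery: "Three trained and qualified health coaches will deliver the coaching sessions". Of the coaches it adds that "they will be monitored by the researchers throughout the period of delivery of the intervention". Section 2.8.3 gives the comparator: "Control group participants will receive only the usual care".

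On data collection, section 2.9 gives interviews and questionnaires to an independent interviewer who is trained and supervised by the researchers: "The interviewer will remain blind to the intervention details, process, and activities". Section 2.9.6 says of the clinical measures: "Quantitative data will be generated and collected by the researchers". The same sentence continues that the centre's health professionals support this, and it lists HbA1c, BMI, blood pressure, weight and waist circumference. Section 2.9.6 also has a health practitioner, such as a laboratory specialist, take the in vitro measures.

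**The concern.** The label in section 2.2 and the procedure in section 2.6 cannot both be true. Keeping the allocation undisclosed until baseline is complete protects the baseline data. It does not blind anyone afterwards, and the secondary outcomes are compared after 3 months.

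The label tells a reader that reporting and detection bias were controlled by design. Efficacy is secondary here, but the results are put to use. Section 1.1.1 lists estimating the effect size, and determining the sample size of the larger trial from this study's findings, among the primary objectives. Section 2.9.2 says that changes in the outcomes will help judge whether the intervention is effective. An effect estimate inflated by participants who know they were coached could therefore pass into the planning of the full trial under a label that suggests this was prevented.

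**Working it through.** No formula applies. The check goes through each role and asks what the article states about knowledge of allocation after the baseline assessment.

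- **Participants:** unblinded, stated in section 2.6. The arms also differ visibly: six coaching sessions (section 2.8.2) against usual care only (section 2.8.3), with no sham or attention control described.
- **Coaches:** unblinded by the nature of the intervention (section 2.8.2).
- **Researchers:** unaware before the baseline assessment (section 2.6), and the article is silent afterwards. They monitor the coaches throughout delivery (section 2.8.2), and section 2.9.6 lists field notes and recordings of coaching sessions among the study data. Unblinding is likely, but it is an inference.
- **Interviewer:** blind to the details, process and activities of the intervention (section 2.9). Allocation is not mentioned. The post-intervention interviews ask about the intervention experience (section 2.9.1, Acceptability), which would tend to reveal the group.
- **Laboratory or health practitioner taking in vitro measures:** no blinding stated either way (section 2.9.6).

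Result: of five roles, two are unblinded (participants as stated, coaches by design), and none of the other three is stated to be blind to allocation after baseline. Suppose the interviewer were in fact kept unaware of allocation. One role would then be masked, for part of the data, and participants would still have been told their group. The label would still fail.

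The seven secondary outcomes in section 1.1.2 divide as follows:

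- Self-efficacy and self-management (2 of 7) are self-reported by participants who know their group. This exposure follows directly from section 2.6.
- Blood pressure, waist circumference, weight and BMI (4 of 7) are taken by an observer. Waist and blood pressure depend most on that observer. Exposure depends on who measures at the endpoint and what that person knows, which the article does not say.
- HbA1c (1 of 7) is a laboratory value and is largely protected from assessor influence.

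2 + 4 + 1 = 7. The document gives no figure from which to size the bias in any of them.

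**The case against.** The strongest defence is that an unblinded trial of a behavioural intervention is normal, and that section 2.6 openly says participants are told their group, so a careful reader is not misled. The first half stands: the lack of blinding is not itself a defect. The second half does not rescue section 2.2. It concedes that the label is false. Nor can a fuller protocol behind the article make participants blind once they have been told.

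A second defence is that little depends on blinding. This stands in part. The criteria in Table 4 (consent, recruitment, retention, adherence) need no blinded assessment, efficacy is secondary, and section 3.1 describes it with means and standard deviations. Satisfaction with the coaching could not be blinded under any design. What remains is the use of the effect estimate in section 1.1.1.

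Several stronger readings are tempting and are not supported:

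- *Nobody is blind at the endpoint.* The article is silent on researchers after baseline and on laboratory staff throughout. Silence supports only the statement that no role is said to be blind.
- *Unblinded researchers take the endpoint waist and blood pressure.* Section 2.9.6 does not say who takes each measurement, mentions support from centre staff, and uses the researchers as a collective term. It does not show that those who monitor the coaches are those who measure.
- *The researchers sit in on coaching sessions, or collect every outcome.* Section 2.8.2 says that coaches are monitored and does not say how. Questionnaires belong to the interviewer.
- *The interviewer's blinding claim is broken.* The claim covers intervention content, not allocation. Whether questionnaires come before or after the interview is not stated, so contamination of the scores would be an assumption.

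**Conclusion.** The concern holds as an internal contradiction. The double-blind property claimed in section 2.2 does not exist under section 2.6, and no role is stated to be blind to allocation after baseline. This conclusion needs no assumption. That the researchers are unblinded at the endpoint is likely, because they monitor the coaches and are also described as collecting the clinical data, but this is an inference.

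The consequence is real but limited. It certainly touches the two self-reported outcomes, it may touch the four observer-taken ones, and it hardly touches the HbA1c assay. It does not affect the progression criteria or the sample of 30. The bias cannot be quantified from the document. The label should be corrected before the effect estimates are reported or carried into the full trial.

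**What to change.** 1. In section 2.2, delete double-blind and describe the trial as open-label, with allocation undisclosed until after the baseline assessment.
2. Claim assessor blinding only for outcomes whose assessor is specified as unaware of allocation. For example, endpoint blood pressure, weight and waist could be taken by existing centre staff who are not involved in the coaching or in the participant's care and are not told the allocation. This condition is needed because section 2.8.1 has centre practitioners agree the target behaviours and section 2.9.1 asks participants' physicians for feedback, so some centre clinicians will probably know who is coached. A general phrase such as assessors unaware where possible could repeat the present error.
3. In section 2.9, have questionnaires completed before the exit interview.
4. State that self-efficacy and self-management are self-reported by participants who know their group, and that effect sizes used to plan the full trial are to be read with that bias in mind.

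The cost is wording, minor reassignment of measurements among staff already at the centre, and a less favourable design label. Only the first and last items are needed to remove the contradiction and its misleading effect. The other two make a partial blinding claim possible.

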### 2.3. Participants

The target population of this study is adult men with T2DM (HbA1c) ≥7.0%. Participants will be eligible for recruitment as per the following criteria:

### 2.4. Eligibility Criteria

Aged >18 years old;The participant diagnosed with T2DM;Haemoglobin A1c (A1c) ≥7.0%;The participant can read and understand Arabic;The participant has access to a personal mobile phone/smartphone;The participant is willing to complete the intervention period;The participant is willing to remain in Riyadh.

Patients are not eligible if they: (1) had physical impairments that prevented them from participating in physical activity, (2) patients are unable to understand or unwilling to give their informed consent.

### 2.5. Recruitment

Recruitment will take place at a primary care centre at KFMC. Advertising for the intervention will use multiple methods, including posters, brushers, social media and through health care provider referrals. Interested individuals will be assessed for eligibility to participate in the intervention. Those who meet the eligibility criteria will be contacted to meet with the research team to briefly explain the study and answer any related questions. Interested individuals will be given a booklet that explained the study and its aims before signing the consent form. Participants will complete a short initial screening assessment, including demographic information and baseline-related laboratory reports.

### 2.6. Randomisation and Blinding

All recruited participants will be randomised on a 1:1 ratio into one of two groups. The randomisation process will be carried out by an independent person out of this study and used a computer to generate random numbers. To minimise selection bias, eligible participants will have an equal opportunity of being allocated to each group. The researchers will remain unaware of which group a participant had been assigned to before the baseline assessment. Participants will be informed which group they have been assigned to after the baseline assessment.

### 2.7. Sample Size

To the best of our knowledge, there was no previous health coaching RCT feasibility study in the field to use as a reference for the sample size. Thus, this study seeks to recruit at least 9% (n = 30) of the sample size required to carry out a full trial [34], with a minimum of 12 participants in each group [35]. Participants will be randomly allocated to either the coaching group (n = 15) or the control group (n = 15).

### 2.8. Intervention

#### 2.8.1. Intervention Content (Intervention Group)

Health coaching in the context of T2DM can be characterised as a complex intervention due to the various direct and indirect interacting components that impact the intervention’s outcomes. Health coaching, as a complex approach, has arisen from multiple different behaviour change theoretical bases. While complex intervention is not a straightforward study with direct clear causal and effects interaction, several crucial requirements and careful considerations are required when replicating it. This is aside from the fact that health coaching combines various disciplines such as psychology with numerous theories into one approach. Thus, we used the model and Theoretical Domains Framework (TDF) as guidance in adapting the intervention into a new context, namely Saudi Arabia.

The intervention is drawn on the COM-B model and TDF to provide a precise and systematic description of the health coaching content. COM-B model is the central part of the Behaviour Change Wheel (BCW) that helps in identifying the interactive process from; capability, opportunity, and motivation required to bring about the desired behaviours of an intervention [23]. The Theoretical Domains Framework (TDF) is a tool to provide further comprehensive explanations that link the COM-B model for a better understanding of the needed changes and determining the target behaviour [36]. Several barriers have been identified based on a literature review of previous work and what needs to be changed to bring about the desired outcomes. In addition, different target behaviours have been identified that would lead to adopting a healthy diet and lifestyle as advocated by UK lifestyle guidelines [37]. To the best of our knowledge, there are no evidence-based guidelines in SA for T2DM to adopt a healthy diet and lifestyle. Therefore, the UK lifestyle guidelines will be used due to their relevance to the Saudi context [5,37]. The UK lifestyle guideline will be utilised to identify the possible behaviour targets. In order to specify target behaviours, a discussion will be conducted with health practitioners at the health centre (the intervention setting), including a dietician, to reach an agreement on the behaviours list. The discussion helps assess and prioritise the target behaviours according to their potential effects, and possibility to be measured and achieved [38].

The four proposed behaviour targets are [37]:Decrease carbohydrate intake for each meal;Use unsaturated fats as much as possible (avoid saturated fats);Do exercise for 30 min, five days in a week;Monitor waist circumference, maintain it below (80 cm for women and 94 cm for men).

Based on the results from COM-B and TDF behaviour analyses, different intervention functions will be identified and linked to the key barriers (see Table 1). Next, the intervention functions will be assessed for their suitability based on APEASE criteria; affordability, practicability, effectiveness/cost-effectiveness, acceptability, safety/side effects and equity, as recommended by the BCW guide [23].

As recommended by BCW guide, multiple BCTs could be used for each identified intervention function [23]. The BCW guide suggests the most common and less frequently used BCTs for each intervention function. Different possible BCTs were identified and included as a part of intervention functions to deliver certain coaching activities and address the key barriers. The BCW guide, previous literature review analysis, including recent systematic review results for the most effective BCTs associated with a clinically significant reduction in HbA1C were all used to help in selecting BCTs. Some BCTs were selected as per the competencies of health coaching as recommended by ICF and the intervention-underpinning theories. As advocated by [39], the BCTs have been selected and matched to the underpinning theories used in this study motivational interviewing (MI) and the transtheoretical model (TTM). The BCTs used that match the MI techniques are presented (see Supplementary File S2) [40]. In addition, other BCTs used in the health coaching intervention that match the TTM are presented (see Supplementary File S3) [41]. All the identified BCTs were assessed according to APEASE criteria to ensure the possibility of using them in the intervention context. Table 2 maps the BCTs selected and their link to the key barriers and intervention functions.

In summary, a total of 29 BCTs will be used to carry out the content of health coaching, including the activities to achieve the desired outcomes. Out of 29 BCTs, 16 BCTs were identified from the intervention underpinning theories (IM and TTM) [40,41]. In addition, four BCTs were identified and showed effectiveness in reducing the levels of HbA1c [42]. Additional nine BCTs were included that match the provided skills of health coaching.

#### 2.8.2. Intervention Procedure

Three trained and qualified health coaches will deliver the coaching sessions. They all will receive training on the intervention curriculum (see Table 2). Additionally, they will be monitored by the researchers throughout the period of delivery of the intervention. The intervention consists of 6 sessions that will be delivered biweekly via face-to-face meetings and telephone coaching over a 3-month period. Intervention group participants will be contacted fortnightly and coached using a combination of different methods; in person, by phone, and by smartphone (e.g., secure messaging such as WhatsApp) while the control group participants only receive the usual care for participants with T2DM with includes general lifestyle advice. Face-to-face coaching is only conducted at baseline and in the third month of the intervention for 30–45 min coaching sessions. In addition, 10–15 min telephone coaching will be delivered for the other four sessions (see Figure 1). 

The health coach works as an ally to enable participants to effectively engage in their self-care needs and address potential self-management barriers. They will be provided with different tools, including a patients’ progress tracker, coach notes log and a coaching log to help them run each coaching session. Participants will be given the opportunity to learn and practice significant skills to help them reach target goals through action plans they set for themselves for better self-care [43]. Table 2 illustrates the operationalised protocol and phases of session delivery

